## Abstract

Following the rapid increase of the aging population, health promotion and prevention of physical disability and dementia in older persons are essential for healthy aging. For example, there may be a potential to prevent or reverse cognitive frailty, the co-existence of both physical frailty and cognitive impairment in older persons. However, evidence-based interventions targeting the prevention or potential reversibility of cognitive frailty among community dwelling older adults are scarce. In this paper, we described the rationale, development and delivery of a multi-domain intervention comprising multi-component physical exercise prescription, cognitive training, dietary counseling and promotion of psychosocial support, called the WE-RISE trial. The aim of WE-RISE intervention is to potentially reverse cognitive frailty. This is a two-armed, single blinded, randomized controlled trial conducted over a duration of 6 months, at senior citizen activity centers within the Klang Valley, Malaysia. Ambulating, community dwelling older adults aged 60 years and above with cognitive frailty are randomized into two groups; (1) intervention group: which receives an instructor based “WE-RISE” intervention for the first 3 months, and then a home-based “WE-RISE at Home” intervention for the following 3 months; (2) control group: usual care with no modifications to their daily routine. Primary outcome is cognitive frailty status and secondary outcome include physical function, cognitive performance, nutritional status, psychosocial status and quality of life which are obtained during baseline screening and subsequent follow ups at 3rd and 6th month. Description of the intervention is done using the template for intervention description and replication (TIDieR) checklist. This trial protocol has received approval from Research Ethics Committee of Universiti Kebangsaan Malaysia (UKM PPI/111/8/JEP-2018-558) and the Department of Social Welfare Malaysia (MyResearch Reference: JKMM 100/12/5/2: 2018/405). Trial registration number: ACTRN12619001055190.

## Introduction

The average lifespan of an individual has globally increased. Malaysia is expected to be labeled as an “aged nation” by the year 2035 with 15% of its' country comprising of older persons (1) Older persons remain predisposed to adverse health outcomes resulting in reduced quality of life and increased cost of healthcare (2). Frailty and cognitive impairment have been enlisted as two of the four modern “giants of geriatrics,” followed by sarcopenia and anorexia of aging (3).

Physical frailty, a prevalent clinical syndrome is manifested due to age-related degeneration of multiple systems leading to rapid health decline in older persons (4, 5). Older persons with frailty are more vulnerable and are susceptible to events such as falls, physical disability, disruption of functional independence, prolonged hospitalization, institutionalization, and fatality (5, 6). Recognized as an intermediate stage between robust and disability among older persons, frailty can be identified with the presence of unintentional weight loss, fatigue, weakness, slow motor performance, and physical inactivity as outlined in the Cardiovascular Health Study (CHS) (6).

While, mild cognitive impairment (MCI) is a symptomatic, pre-dementia phase, characterized by self-reported clinical concern, and objective memory deficits, but without functional decline (7). The occurrence of cognitive decline has been associated with vascular disease, metabolic disorder, trauma, infectious diseases, depression and polypharmacy (8). Marked changes in cognitive function may commence as early as between 3 and 7 years preceding the diagnosis of MCI (9). Hence MCI, a prodromal symptom of dementia is a primary target for early intervention to prevent or delay the progression into an irreversible state of cognitive impairment (10).

Amongst the Malaysian community dwelling older population, the prevalence of frailty and pre-frailty was reported to be 8.9 and 61.7%, respectively (11), whereas MCI is prevalent at 16% (12). Prevalence of frailty and pre-frailty has been reported to be much higher amongst institutionalized older persons at 40.7 and 56.6%, respectively, with cognitive impairment as a predictor (13). The stark contrast in prevalence between community dwelling and the more vulnerable institutionalized population is attributed to poorer health outcomes; mainly severe physical and cognitive impairments (14). There is a cyclic relationship between physical frailty and cognitive impairment, whereby the disintegration of one construct is likely to result in the consequent declination of the other (15, 16). Aimed at coalescing both constructs, the “cognitive frailty” syndrome among older adults was established in 2013 (17). Cognitive frailty is defined as a “heterogeneous clinical manifestation characterized by the simultaneous presence of physical frailty and diagnosis of cognitive impairment excluding the presence of concurrent Alzheimer's disease (AD) or other dementias” (17).

Prevalence of cognitive pre-frailty and cognitive frailty among community dwelling Malaysian older population was reported at 37.4 and 2.2%, respectively (18). Results from a longitudinal study reported the incidence rate of cognitive frailty in Malaysia at 7.1 per 100 person-years among older adults who were non-cognitively frail at baseline (19). The rate of incidence increased with increasing age among older adults aged 75 years and above, whereby it doubles every 10 years; estimated at 13.34 per 100 person-years (19). Research concerning cognitive frailty in the Malaysian context is a recent development and there is currently no available local intervention addressing this prevalent condition.

At present, physical frailty and cognitive impairment are often separately studied and addressed, despite the evidence that both are correlated (17). Although, cognitive frailty has been deduced to be “potentially reversible,” a specific intervention targeted at addressing this condition in the community and home based setting remains unestablished (20). Thus, we aim to examine the effectiveness of a newly developed multi-domain intervention for possible reversal of cognitive frailty among Malaysian community dwelling older persons.

## Methods and Materials

### Rationale for the Development of a Multi-Domain Intervention

The rationale for the development of this intervention is to address the multi-factorial predictors of cognitive frailty. This include poor physical fitness, functional dependence, depression, lack of social support, and nutritional deficiency (18, 19). There is substantial evidence advocating for the development of an intervention employing a multi-domain approach in the attempt to delay or reverse this condition; rather than a singular approach (21).

Older persons living with lower socioeconomic status are at higher risk of being frail and care dependent due to malnutrition, poor physical health practices, inevitably subjecting them to disability, and mortality (22). Moreover, these older adults are more inclined to have decreased cognitive function possibly due to lower education levels (22). Within the community-based rehabilitation settings, there is yet to be a complimentary, self-sustaining, low cost intervention for these older persons. Hence, the development of this multi-domain intervention aims to bridge this existing gap.

### Components of the Multi-Domain Intervention

Evidence of the effectiveness of a multi-domain intervention in addressing cognitive frailty is currently unavailable. However, multi-domain intervention approach has been utilized with positive outcomes for physical frailty and cognitive impairment separately. For example, in the study by Ng et al. (23), a multidomain approach combining nutritional, physical and cognitive interventions significantly reduced frailty among pre-frail and frail older adults. Similar intervention has also been aimed at delaying cognitive impairment among older persons at risk of cognitive decline in the 2-year Finnish Geriatric Intervention Study to Prevent Cognitive Impairment and Disability (FINGER) trial which consisted of nutritional guidance, exercise, cognitive training and social stimulation as well as monitoring metabolic and vascular risk factors (24). It is noteworthy that these interventions were client-tailored and not community-based. Inclusion of physical activity, cognitive training, nutritional and dietary guidance, emotional recovery, and social support via a multi-faceted approach are the recommendations for potential reversibility of the cognitive frailty status (20, 25). These evidence and recommendations served as the foundation for the development of our current multi-domain intervention for reversible of cognitive frailty.

Exercise training has been demonstrated to be beneficial in improving frailty symptoms and cognitive function, in addition to being cost effective (26, 27). The evidence corroborates with the existing notion that exercise has the potential to reverse frailty by improving physical function (28). Similarly, exercise, specifically aerobic training was concluded to be effective in sustaining cognitive function and may delay the occurrence of cognitive decline in a systematic review (27).

While, cognitive training is beneficial in training or re-training relatively well-defined cognitive abilities such as information processing, attention, memory or problem solving via the concept of neuroplasticity (29). Taking this concept into consideration, cognitive based exercises involving guided practice structured tasks have been incorporated into interventions to enhance cognitive function (29, 30). Although, lacking high impact evidence, cognitive training has been used in combination with other domains of intervention (physical activity, socialization or healthy diet) to reduce the risk of cognitive decline and progression into dementia (29, 31).

In regard to nutritional interventions, it is important in addressing cognitive frailty as malnutrition is a contributor to the onset and progressive worsening of cognitive frailty and other related co-morbidities (25). Deficiency of protein, vitamin D, vitamin B12, inadequate calorie intake or even over-eating in middle age have been enlisted as several factors leading to sarcopenia, weight loss, fatigue and cognitive decline among older adults (18, 25, 32). There is evidence to suggest that nutritional interventions promoting a continuous practice of balanced dietary patterns, could delay cognitive frailty (25). Additionally, combination intervention such as exercise and nutrition is strongly recommended as compared to nutritional intervention alone among frail and cognitively impaired older adults (33).

Generally, healthy or successful aging include physical, mental, and psychosocial well-being (34). Factors such as positive self-esteem, self-achievement, self-worth, and self-efficacy are associated with positive health outcomes among older persons (34). An association between poor psychosocial status, cognitive impairment, and physical frailty has been established (21). Notably, incorporating elements of fun, social inclusion, and enjoyment in older persons with frailty resulted in improved frailty scores, delaying functional decline, improved quality of life as well as psychosocial well-being (35). Promotion of social interaction via group-based interventions have also shown favorable outcomes amongst older persons with cognitive impairment and frailty (21, 36).

### Development and Selection of Specific Intervention

An evidence-based exercise program for older adults with cognitive frailty is not available. Thus, we developed a multi-component exercise program based on the combination of the available evidence. Firstly, the components of aerobic exercise, progressive resistance training, balance and flexibility were selected as it addresses the frailty criterion of weakness, slow motor performance, low physical activity, and fatigability (26, 37). Next, we benchmarked the evidence in an umbrella systematic review of systematic reviews (total of 58 RCTs) evaluating the effectiveness of exercise-based interventions among those with pre-frailty and frailty (26). In this review, it was concluded that multi-component exercise training was the most effective form of exercise-based intervention among pre-frail and frail older persons as it improved physical performance, specifically muscle strength, gait speed, and balance (26). The proposed outline of a multi-component exercise program targeting older persons with frailty should encompass progressive resistance training, aerobic, balance, and flexibility training. The frequency of exercise sessions was suggested up to thrice weekly for a duration of between 45 and 60 min per session at moderate to high intensity. Effective exercise program should be carried out for at least 10 weeks or more (26).

This population is also vulnerable to a plethora of unfavorable health outcomes, including the risk of falls (6). So, we adapted the design and progression of exercise prescription of the Otago Exercise Program (OEP) (38) in respect to progressive strengthening and balance exercises. OEP is an evidence-based falls prevention program targeting community dwelling older adults which has yielded positive outcomes in overall improvement in physical function and a 35% decrease in falls among older persons with frailty (39). Further modifications of balance exercises were made to cater for functional training. These included improving performance in task accomplishment which often require multi-tasking when carrying out activities of daily living. The aim is to improve specific balance related ability such as regaining postural stability following perturbation, reaching upwards or downwards multiple times to collect household objects or even the ability to avoid obstacles while walking and talking (40). Lastly, the exercises were adjusted in accordance to the ACSM consensus recommendations for physical activity among older adults (41).

As for cognitive intervention, it is commonly delivered via technology such as computer-based training software or more recently commercialized packages for the use on smart devices (42). However, a non-technological and more traditional method of interactive cognitive training has also been shown to improve attention and memory among older Singapore population with frailty (23). We believed that this approach of cognitive training may be more sustainable and feasible as a low cost, community-based intervention for the purpose of our present study. Moreover, the targeted older persons for the present intervention expressed that they were not in favor of using technological gadgets in our needs assessment discussion.

The domains of cognition namely short-term memory, attention, information processing skills, perceptual organizational tasks, reasoning and logic, and problem-solving abilities were selected for cognitive training in our present intervention. This selection was based on the existing literature among older adults with cognitive impairment (23, 31, 43). We included “Pen to Paper” tasks such as “spot the difference,” mazes, matrix reasoning, and jigsaw puzzles. These tasks have been included as cognitive training resulting in enhanced cognitive function as it tackles multiple domains of cognition (visual perception, orientation perceptual reasoning, cognitive speed), and promotes an increase of brain reserve whilst preventing emotional distress which negatively impacts cognitive aging (23, 44). We deduce that this hands-on approach of cognitive training is not only effective in improving cognitive function but also beneficial in promoting social engagement as an activity of leisure.

For nutritional intervention, the existing interventions to address cognitive impairment or frailty consist of a wide range including a variety of supplementation, specialized diet and single or multi-nutrient intervention (33, 45, 46). As an alternative, dietary counseling, an inexpensive, and straightforward intervention and has been found to substantially reduce the risk of malnutrition among older adults (33). Hence, dietary counseling with education on healthy eating habits was opted as the nutritional intervention in our present study to allow older persons to sustain their healthy eating patterns as it is personalized to locally available and affordable produce.

Group directed intervention was the choice for the delivery of our present multi-domain intervention. This is because it is known to promote social participation, besides improving adherence to physical activity, psychological factors and social relationships; which further advocates that group-based intervention is key as a means of incorporating psychosocial well-being among older adults (47).

### Description of the WE-RISE Intervention (TiDieR Checklist)

#### Brief Name

The “WE-RISE” intervention stands for: Warga Emas - Resilient mInd and muScle Exercise. “Warga Emas” translates to Senior Citizens in the Malay language. The terms “resilient mind and muscle” was selected as we aim to reverse impaired physical and cognitive status of the older persons with respect to cognitive frailty.

#### Where: Intervention Location

Targeting community dwelling older adult population, we screened and recruited registered members of the Activity Centers for Older Persons; known locally as “Pusat Aktiviti Warga Emas” (PAWE) for the present study. PAWEs has been set up across the nation under the Malaysian Department of Social Welfare (48). These activity centers provide a social space promoting active participation and involvement of older persons within the community (48).

#### Intervention Providers

The exercise, cognitive and psychosocial component of the intervention was administered by a qualified physiotherapist with geriatric rehabilitation background (primary research coordinator). The physiotherapist in charge underwent training which included background to the adversity of cognitive frailty, rationale of the intervention, practical session of the intervention and participant safety moderated by Physiotherapist and Clinical Psychologist lecturers (research team members). The dietary component of the intervention was administered by a trained clinical dietician under the supervision of a Professor in Nutrition and Dietetics (research team member).

#### Procedure and Materials

In this randomized controlled study, participants were screened at baseline via face to face interview using a structured questionnaire for sociodemographic and clinical characteristics, psychosocial and functional status, cognitive function, quality of life and dietary intake. Anthropometry and physical performance measurements were objectively assessed. All assessments were conducted by qualified research assistants who were trained together. Inclusion criteria of this study were: Malaysian, community dwelling, aged 60 years and above, able to ambulate independently and classified to have cognitive pre-frailty or cognitive frailty. Older persons who were physically robust, diagnosed with terminal illnesses, major psychiatric illnesses, classified to have mild to moderate dementia, unable/refused to participate in the intervention, or already participating in other programs or on-going trial were excluded from the present study. The primary and secondary outcomes are as outlined.

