##### Primary outcome: cognitive frailty

This study operationalized cognitive frailty as proposed by Kelaiditi et al. (17) using Fried's criteria as outlined in the Cardiovascular Health Study to define physical frailty and the Clinical Dementia Rating Scale (CDR) to define objective cognitive impairment. The presence of one or two of the Fried's criteria was defined as pre-frailty, whilst the presence of three or more was defined as frail and a score of 0.5 on the CDR is defined as mild cognitive impairment (MCI) (17). Collectively, participants who had a combination of pre-frailty/frailty and MCI were categorized as cognitive frailty (Table 1).

**Table 1 T1:** Classification of cognitive frailty groups.

	**Criteria**	**Categorization**		
		**Robust**	**Cognitive pre-frailty**	**Cognitive frailty**
**Frailty** Fried et al. (6)	*Shrinking*: Unintentional weight loss of more than 5 kgs	0	1–2 Criteria	≥3 Criteria
	*Weakness*: Assessed with hand grip strength and adjusted for gender and body mass index against original cut-off points.			
	*Slowness*: Assessed with 5-meter gait speed test, adjusted for gender and height against original cut off points.			
	*Exhaustion*: Identified with two items from the CES-D scale.			
	*Low physical activity*: Identified by low scores of the PASE.			
**Cognitive impairment** Kelaiditi et al. (17)	Clinical Dementia Rating Scale score	0	0.5	0.5

*CES-D, Center for Epidemiologic Studies Depression Scale; PASE, Physical Activity Scale for Elderly*.

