##### Randomization

Participants with cognitive pre-frailty or cognitive frailty were randomized into intervention and control groups. Simple randomization was executed using the Research Randomizer computer program by the primary research coordinator (59). The trial flow is as illustrated in Figure 1. In this single blinded study, research assistants involved in data collection for the baseline and follow up outcome measures to prevent bias were blinded of the groups. Primary research coordinator was not involved in data collection. In order to minimize contamination between the intervention and control groups, an arrangement was made with the participating PAWEs to allow private and scheduled use of the facility on days that are not open for member activities.

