The WE-RISE intervention hopes to provide easier accessibility whilst enabling “age-friendly” health care delivery. If the intervention is found to be effective, the community-based nature of the intervention delivery may also be of lower cost as compared to the process of obtaining standard healthcare. Furthermore, it is not specific to the subset of older persons from lower socioeconomics but can also be applied amongst all walks of life and be practiced as a preventative strategy. The effectiveness and cost effectiveness of the WE-RISE intervention as compared to usual care on the reversal of cognitive frailty status among community dwelling older adults will be reported at the end of the trial. It is hoped that WE-RISE which is a multi-component and domain intervention will not only be beneficial in addressing cognitive frailty but also physical activity and general health in older persons.

In conclusion, we hope the address the need for a comprehensive and feasible intervention which is also sustainable in terms of delivery and cost for the well-being of older persons with cognitive frailty. The WE-RISE is versatile and can be administered within the community as well as a hospital or nursing home setting by most exercise instructors or primary healthcare practitioners with training.

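### The aim is stated as reversal of cognitive frailty, but on the article's own prevalence figures about 86–94% of eligible people would be expected to be cognitively pre-frail

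*Protocol article*

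**What the plan says.** The Abstract of the Protocol article gives the aim as potential reversal of cognitive frailty and describes the people randomized as older adults with that condition. The Discussion promises a report on reversal of cognitive frailty status in community dwellers.

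The inclusion criteria under Procedure and Materials take in two stages: "able to ambulate independently and classified to have cognitive pre-frailty or cognitive frailty". The Randomization section pools them: "Participants with cognitive pre-frailty or cognitive frailty were randomized into intervention and control groups. Simple randomization was executed". No intended mix of the two is given.

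The section on the primary outcome uses the term in two senses. It first divides physical frailty by count: "The presence of one or two of the Fried's criteria was defined as pre-frailty, whilst the presence of three or more was defined as frail". Table 1 carries this division into separate columns for cognitive pre-frailty and cognitive frailty, both with a Clinical Dementia Rating of 0.5. The text just before the table merges them: "Collectively, participants who had a combination of pre-frailty/frailty and MCI were categorized as cognitive frailty".

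The Introduction uses the narrower sense: "Prevalence of cognitive pre-frailty and cognitive frailty among community dwelling Malaysian older population was reported at 37.4 and 2.2%, respectively". It also gives the components: "the prevalence of frailty and pre-frailty was reported to be 8.9 and 61.7%, respectively (11), whereas MCI is prevalent at 16"%. For residents of institutions it reports frailty and pre-frailty as "much higher amongst institutionalized older persons at 40.7 and 56.6%, respectively, with cognitive impairment as a predictor". The Discussion closes by saying that the programme "can be administered within the community as well as a hospital or nursing home setting".

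**The concern.** A reader told that the programme reverses cognitive frailty would look to Table 1 or the Introduction for the meaning, and would take it to cover people with three or more Fried criteria. If nearly all participants have one or two, the evidence comes mainly from a milder stage that the article names differently in both places.

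The stages may also differ in their chance of the outcome. The article does not say which transition counts as reversal. If it means reaching Table 1's robust column, then on the frailty component a pre-frail person must lose one or two criteria and a frail person at least three. The baseline mix would then affect both the overall reversal rate and the population to which it applies.

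**Working it through.** The article states no sample size and no expected mix, so there is no design figure to reproduce. The check is a projection from the prevalence figures in the Introduction.

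**Expected share of each stage among eligible people**

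| Basis | Calculation | Pre-frail | Frail |
|---|---|---|---|
| Cognitive pre-frailty 37.4%, cognitive frailty 2.2% | 37.4/(37.4 + 2.2) = 37.4/39.6 | 94.4% | 5.6% |
| Physical pre-frailty 61.7%, frailty 8.9% | 61.7/(61.7 + 8.9) = 61.7/70.6 | 87.4% | 12.6% |
| Both stages together capped at the 16% prevalence of mild cognitive impairment (MCI), cognitive frailty 2.2% | (16 − 2.2)/16 | 86.3% | 13.8% |

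Rounding of the inputs moves the first row only between 94.3% and 94.6%. The other rows are needed because the figures do not fit together. Both stages require MCI in Table 1, yet their combined prevalence, 37.4 + 2.2 = 39.6%, exceeds the 16% given for MCI. The sources probably used different definitions or populations. The supportable range is about 86–94% pre-frail.

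**Expected number with three or more criteria** (total N is assumed; frail count = N × frail share)

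| Assumed N | At 5.6%: total (per arm) | At 13.8%: total (per arm) |
|---|---|---|
| 60 | 3.3 (1.7) | 8.3 (4.1) |
| 100 | 5.6 (2.8) | 13.8 (6.9) |
| 200 | 11.1 (5.6) | 27.5 (13.8) |
| 300 | 16.7 (8.3) | 41.3 (20.6) |

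With three frail participants in an arm and one reversal, the exact 95% interval for the reversal proportion is about 1% to 91%. A result by stage can therefore only be descriptive.

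**Chance imbalance under simple randomization.** Let the frail count be binomial with N = 100 and probability 0.0556, each frail participant falling to either arm with probability 0.5. One arm then has at least twice the other's frail count in about 56% of allocations, and at least one arm has none in about 12%. At a 13.8% share, the two-fold figure falls to 27%.

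**Effect of that imbalance on the primary comparison.** Assume N = 100 (50 per arm), 30% reversal, and a 30-point difference in reversal between stages. None of these comes from the article.

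- SD of the between-arm difference in frail share, at 5.6%: √(2 × 0.0556 × 0.9444/50) = 4.6 points.
- SD of the resulting shift in the reversal difference: 0.30 × 4.6 = 1.4 points.
- Ordinary standard error of the reversal difference: √(2 × 0.3 × 0.7/50) = 9.2 points.
- Share of variance: (1.37/9.17)² = 2.2%.
- At a 13.8% share the SDs are 6.9 and 2.1 points, and the share of variance is (2.07/9.17)² = 5.1%.

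Large relative imbalance in a small stage is thus common but moves the overall comparison little.

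**Institutional residents.** Among those not robust, the frail share is 40.7/(40.7 + 56.6) = 41.8%, against about 6–14% expected here.

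**The case against.** The strongest objection is the merging sentence under the primary outcome. On that definition every eligible participant is cognitively frail and the aim is addressed in the whole sample. This stands. A reader might infer from 94% that the trial answers its question in almost no cognitively frail people; that is true only under Table 1's narrower column. What remains is that the article uses one term in two senses, so a claim of reversal does not show which stage it rests on.

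The projection is also soft. The prevalence figures describe the general community, whereas recruitment is from members of activity centres. A reader might infer that requiring independent ambulation can only lower the frail share. The documents do not establish this: the rationale also points to older persons of lower socioeconomic status, whom it describes as at higher risk of frailty.

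The nursing-home sentence concerns where the programme can be delivered and by whom. The planned report is limited to community dwellers. It should not be read as a claim of proven efficacy in institutions.

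A reader might also infer that simple randomization without quota or stratification biases the comparison. It does not: allocation is unbiased, the test's error rate covers chance imbalance, and on the assumptions above stage imbalance accounts for only 2–5% of variance. Stratification and quotas are design preferences. A stage covariate and results by stage are often left to an analysis plan, which is not at hand, so their absence from the article is not a fault.

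**Conclusion.** The point holds as one about the stated population and claim. On the article's own figures, about 86–94% of eligible people would be expected to have one or two Fried criteria, and a finding of reversal would rest mainly on them. This assumes that the mix among eligible activity-centre members resembles the community figures, which themselves disagree; the enrolled mix could differ. At an assumed total of 100, about 3 to 7 participants per arm would have three or more criteria, too few for a separate conclusion about that stage. The trial's validity is not in question. Adjustment for baseline stage would bring precision and protection from chance imbalance, and would not remove any systematic bias.

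**What to change.** 1. Word the aim and conclusion as effectiveness in ambulant community dwellers with cognitive pre-frailty or cognitive frailty, expected to be mainly pre-frailty. Use the term cognitive frailty in one sense throughout.
2. Adjust the primary comparison of follow-up status for the baseline Fried criterion count, or for stage (1–2 versus 3 or more). Either is available from the baseline classification.
3. Show the baseline mix by arm and the primary result by baseline stage, descriptively and without a separate claim for either stage.
4. Keep the sentence on hospitals and nursing homes as a statement about delivery, and do not carry the effectiveness conclusion over to residents there.

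The cost is some rewording, one covariate and one table, with no new data collection. The downside is a narrower claim.
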